### Baseline data collection

Interviewer-administered semi-structured questionnaire (S2 File) will be used for data collection. The questionnaire will be developed from the review of related local literature [12, 42, 45], and will be pretested and validated for use among the study participants. The oral examinations will be based on the WHO Oral Health Surveys: Basic Methods, 5^th^ Edition [46]. Five trained and calibrated dentists will conduct the interview and oral examinations. The dentists will be trained by an expert in oral epidemiology using the WHO guideline [46]. The questionnaire will be used to collect information on the participants’ sociodemographic characteristics, oral hygiene knowledge, attitude, and practices. While the children will be the main respondents, their parents (preferably mothers) will be called by the research assistants to validate the information provided by the children regarding the sociodemographics and oral hygiene behaviour. The oral examination will assess the participants’ oral hygiene status (simplified oral hygiene index [47]) and their lifetime caries experience [sum of decayed, missing, and filled teeth (dmft/DMFT) [46, 48]]. Based on the simplified oral hygiene index (OHI-S), indexed teeth would be assessed. On the upper jaw/maxilla, the Right and Left First Molar (UR6, UL6) and Right Incisor (UR1) will be assessed. Similarly, both the Right and Left First Mandibular Molars (LR6, LL6) and the Left Mandibular First Incisor (LL1) will be examined in the low jaw/mandible [47]. If any of these teeth are absent, another designated tooth in the segment will be examined [47]. The oral examination will be done using a sterile wooden mouth spatula, probes, and dental mirrors. The oral examination will be conducted near the windows in the school halls, with the participants seated upright facing the window such that the examination is aided by good illumination from natural light. Baseline data collection will be conducted in both study groups (test and control) one week before delivering the interventions.

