## Materials and methods

### Study design

The research is designed to be a cluster-randomised, assessor-blinded, controlled trial with two study groups—intervention and control. The randomised control design was adopted to provide a high level of evidence for the study. The IMB model will form the framework for the study (Fig 1).

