### Post-intervention data collection

There will be three sessions of post-intervention assessments—Immediate, six, and 12 months. The immediate post-intervention assessment will collect information on the participants’ oral hygiene knowledge and attitude immediately after the second session of the intervention is completed. The 6-month post-intervention assessment will be conducted six months after the immediate post-intervention assessment. Information on the participants’ oral hygiene knowledge, attitude, and practices will be collected. Oral examinations will also be done to assess the participants’ oral hygiene status using the simplified oral hygiene index. The 12-month post-intervention assessment will be conducted 12 months after the immediate post-intervention assessment. It will involve oral health examinations to check the participants’ oral hygiene status and dental caries experience (dmft/DMFT), along with assessing the participants’ oral hygiene knowledge, attitude, and practices. The same questionnaire for the pre-intervention assessment will also be used for the post-intervention assessments. However, the immediate post-intervention assessment will not include oral examinations. The questionnaires for 6 and 12 months post-intervention data collection will include a question to assess if the participants have been taught oral hygiene practices (through songs or lectures) by pupils from other schools during the study period. This is to get data on the potential contamination and control for this during the data analysis (sub-analysis).

Figs 2 and 3 show the SPIRIT schedule and Flow diagram for the study, respectively.

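### One pool of five dentists is given both the interviews and the oral examinations, and no role separation is stated for follow-up, so the claimed assessor blinding of OHI-S can be lost school by school

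*Protocol article*

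**What the plan says.** The Study design section describes a "cluster-randomised, assessor-blinded, controlled trial with two study groups". Under Baseline data collection, the questionnaire is administered by interviewers, and "Five trained and calibrated dentists will conduct the interview and oral examinations". The section on validity and reliability again refers to five examiners. No other interviewers or examiners are named anywhere in the article.

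Under Post-intervention data collection:
- "The same questionnaire for the pre-intervention assessment will also be used for the post-intervention assessments".
- The immediate assessment covers knowledge and attitude, has no oral examination, and takes place "immediately after the second session of the intervention is completed".
- At 6 and 12 months the form gains a question on whether participants "have been taught oral hygiene practices (through songs or lectures) by pupils from other schools during the study period". Its stated purpose is to measure contamination and adjust for it.
- OHI-S is scored at both of those visits, and dmft/DMFT at 12 months.

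Eight schools are the units of randomisation, four per arm. Oral hygiene status is the outcome used to size the trial and one of the three primary measures.

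**The concern.** Songs and talks are what distinguish the two arms. A dentist who interviews pupils in a school after the intervention can learn which one that school received, either from the setting or from what a child says. Since the whole school has one allocation, a single cue applies to every pupil examined there afterwards, at that visit and at later ones.

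OHI-S rests on visual judgement, made in natural light as described for baseline, and is cut between 1.2 and 1.3 to define Good. An examiner who knows the arm can shift scores slightly in one direction across whole schools. Such a shift looks exactly like a treatment effect, and no analysis of the collected data can separate the two. The trial relies on assessor blinding to prevent this, so the staffing arrangement should support that claim.

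**Working it through.** **1. The plan's own figure.** The inputs from Sample size determination are P1 = 0.384, P2 = 0.576, power 80%, significance level 5% (two-sided assumed), non-response 10%, attrition 20% and design effect 1.5.
- Unpooled formula: (1.960 + 0.842)² × (0.384 × 0.616 + 0.576 × 0.424) / 0.192² = 102.4 per arm. Then 102.4 × 1.5 / (0.9 × 0.8) = 213.3, so 214.
- Pooled formula: 106 per arm. Then 106 × 1.5 × 1.1 × 1.2 = 209.9, so 210.

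The stated 212 per group lies between these and is reproduced. It does not decide the blinding question, but it gives the target difference of 57.6 − 38.4 = 19.2 percentage points.

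**2. Routes to unblinding, from the text.**
- *Immediate assessment.* Interviews follow directly after the second session. If the five dentists do them, they meet each school's pupils just after a song session or a talk, before any follow-up OHI-S is scored. This route does not depend on the order of tasks at 6 and 12 months.
- *6 and 12 months.* The interview mentions songs and lectures at the same visits as the examination. The question concerns pupils from other schools and is the same in both arms, so disclosure needs a child to misunderstand it or to add something.
- *Spread.* 424 / 8 = 53 pupils share each school's allocation.

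**3. How quickly one disclosure arises (illustration).** Let q be an assumed, independent chance that any one child gives the arm away. The chance of at least one disclosure among 53 is 1 − (1 − q)^53:

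| q | chance |
|---|---|
| 1% | 41% |
| 5% | 93% |
| 10% | 99.6% |

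**4. What a scoring drift would do (illustration).** Assume OHI-S is roughly normal with 38.4% Good, so z = −0.295. The article gives no SD, and 0.6 to 1.2 is assumed. The change in the proportion Good is Φ(−0.295 + drift/SD) − 0.384:

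| Drift in one arm | SD 0.6 | SD 0.9 | SD 1.2 |
|---|---|---|---|
| 0.1 point | 6.5 points | 4.3 | 3.2 |
| 0.2 point | 13.1 points | 8.7 | 6.5 |

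**5. Effect on the test (illustration).** Take no true effect, 38.4% Good in both arms, and an effective size of 212 × 0.72 / 1.5 = 101.8 per arm. If biased scoring adds b to one arm, the rejection rate is Φ((b − 1.96·se0)/se1) + Φ((−b − 1.96·se0)/se1), where se0 is the pooled and se1 the unpooled standard error. For b = 0.05, se0 = 0.0689 and se1 = 0.0688, which gives 0.108 + 0.004 = 11%. For b = 0.02 it is 6%, and for b = 0.10 it is 30%, against a nominal 5%.

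**The case against.** The strongest reply is that the text does not say what a quick reading suggests. A reader might infer that one dentist interviews each child, hears from the answer which arm the child is in, and then scores the teeth. The article supports none of these three steps:
- The sentence on the five dentists describes a pool, at baseline, before any song or talk has been given. It does not say that one dentist does both tasks for the same child. Carrying it to follow-up is an inference.
- No order of interview and examination is given.
- The added question asks about teaching by pupils from other schools. A child in either arm with no such exposure should answer no, and a yes would point to contamination rather than to the child's own allocation.

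In addition, scheduled singing lasts one month, so it ends more than five months before the first follow-up examination. The immediate visit has no oral examination. Detailed blinding procedures may sit in a full protocol that is not shown.

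Most of this stands, and it limits the claim. It does not remove it. The article states the shared pool and the added question, and no other follow-up staff are named. With allocation by school, it matters little whether the same dentist sees the same child, because learning the arm from one pupil is enough for all pupils in that school. The gap of months does not help a dentist who learned the arm at the immediate interview. The conflict between the shared roles and the blinding claim therefore comes from a stated arrangement and is more than missing detail.

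**Conclusion.** The concern holds as a risk, not as a demonstrated failure. The article claims blinded assessment, assigns interviewing and examining to the same five dentists, and adds a question mentioning both arms' methods at the visits where OHI-S is scored. If the baseline staffing carries over, blinding can be lost for whole schools, and the primary outcome can be biased in a way that analysis cannot repair. The documents do not support saying that blinding is broken, or that the interview tells the examiner the arm before scoring.

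The size of the bias cannot be derived from the article. The 3.2 to 6.5 percentage points for a 0.1-point drift rest on an assumed SD, an assumed normal shape and an assumed drift that runs in one direction across an arm. They show that a small drift would matter beside a 19.2-point target, and they are not evidence that a drift will occur. This should be fixed; confidence is moderate.

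**What to change.** From the immediate assessment onward, split the existing five dentists so that nobody scores OHI-S or dmft/DMFT at a school where they have interviewed since the intervention. The simplest form is a fixed split, with the same examiners at all eight schools, which also keeps differences between examiners from lining up with arm. All five are already to be trained and calibrated.

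If the roles cannot be fully split, complete and hand in all examination records at a school before any interview starts there, and keep those dentists out of the immediate interviews at that school. Ordering the tasks within each child is not enough, because it leaves later children unprotected. This fallback is weaker: a dentist who interviews at a school at 6 months could still carry the knowledge into the 12-month examination, unless examiners change schools.

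Two optional additions are to place the contamination question last on the form and to have each examiner record a guess of the school's arm. Neither replaces the split, and cues met elsewhere in a school cannot be ruled out.

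The cost is slightly longer school visits, since fewer dentists examine at a time. No extra staff are needed, and the sample size does not change.

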### Intervention and control groups

The intervention will involve teaching the participants in the test group traditional rhyme (folk songs) on adequate oral hygiene measures and practices. The song was developed in English and Yoruba, the two major Nigerian languages in the two communities. While Yoruba is the primary language of the pupils, they are taught in English. The songs convey health messages, including the importance of twice-daily tooth brushing with pea-size fluoride-containing toothpaste, the need to brush the tongue, and simple tooth brushing techniques using toothbrushes with soft/medium-bristles. The song was co-developed and validated among selected schoolchildren, teachers, and parents/legal guardians [49].

There will be three intervention sessions lasting for one month. During the first session, one of the researchers (OO) will teach selected participants in the test group the two songs (English and Yoruba). Some participants will be asked to sing the songs to confirm if the pupils have learned them. Subsequently, all the participants will be asked to sing the songs several times. The first session of the intervention is estimated to last 40 minutes. The participants will be asked to continue singing the songs every morning in the school for one month, under the supervision of a teacher. This will be monitored through daily visits to the schools by designated research assistants to confirm that the participants are singing the songs as expected. The second session will take place two weeks after the first, and the researcher will ask the participants to sing the songs as a group several times. Similarly, the third session will take place two weeks after the second session (one month after the first session) and the students will also sing the songs in the presence of the researcher (OO). The second and third sessions are estimated to last for 20 minutes.

The participants in the control group will be exposed to conventional health education on adequate oral hygiene practices conducted by the dentist [50]. Similar to the test group, there will be three intervention sessions. The first session will last for 40 minutes and will involve expert-led health talks and question and answer with the participants. The second and third sessions will also take place after two and four weeks, respectively. The follow-up sessions will involve revising the oral health messages with the participants, lasting for about 20 minutes each. None of the participants (control and test groups) will be denied access to oral health talks that they may be exposed to away from school.

### Post-intervention data collection

There will be three sessions of post-intervention assessments—Immediate, six, and 12 months. The immediate post-intervention assessment will collect information on the participants’ oral hygiene knowledge and attitude immediately after the second session of the intervention is completed. The 6-month post-intervention assessment will be conducted six months after the immediate post-intervention assessment. Information on the participants’ oral hygiene knowledge, attitude, and practices will be collected. Oral examinations will also be done to assess the participants’ oral hygiene status using the simplified oral hygiene index. The 12-month post-intervention assessment will be conducted 12 months after the immediate post-intervention assessment. It will involve oral health examinations to check the participants’ oral hygiene status and dental caries experience (dmft/DMFT), along with assessing the participants’ oral hygiene knowledge, attitude, and practices. The same questionnaire for the pre-intervention assessment will also be used for the post-intervention assessments. However, the immediate post-intervention assessment will not include oral examinations. The questionnaires for 6 and 12 months post-intervention data collection will include a question to assess if the participants have been taught oral hygiene practices (through songs or lectures) by pupils from other schools during the study period. This is to get data on the potential contamination and control for this during the data analysis (sub-analysis).

Figs 2 and 3 show the SPIRIT schedule and Flow diagram for the study, respectively.

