**Materials and methods:**

This is a school-based, assessor-blinded, two-arm cluster-randomised controlled trial that will assess the effectiveness of oral hygiene messages delivered through traditional rhyme (folk song) on children’s oral hygiene knowledge, attitude, practices, and oral hygiene status in two rural communities (Igboora and Idere) in Nigeria. The study will involve a minimum of 424 participants (aged 7–9 years) selected from eight primary schools using the cluster sampling technique. Four schools will be randomised into the test group to receive oral hygiene messages through folk songs, and the participants will sing the song for two weeks. The other four schools will be assigned to the control group, and the participants will receive the usual oral health talk on oral hygiene practices by a dentist. The participants’ oral hygiene knowledge, attitude, practice and status will be assessed at baseline, immediate, six, and twelve-month post-intervention. A modified World Health Organization (WHO) Children’s oral health survey questionnaire will be utilised for data collection. Oral examinations will be conducted to assess the participants’ dental caries experience and oral hygiene status using the dmft/DMFT and simplified oral hygiene indices, respectively.

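### The immediate post-intervention assessment is set at week 2 of a four-week intervention, and the abstract halves the singing period

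*Protocol article*

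**What the plan says.** The Protocol article, under *Intervention and control groups*, describes the test arm's course in these words: "There will be three intervention sessions lasting for one month". Session two comes two weeks after session one, and "the third session will take place two weeks after the second session (one month after the first session"). Between sessions the pupils are to "continue singing the songs every morning in the school for one month", supervised by a teacher. The control arm follows the same session calendar: "The second and third sessions will also take place after two and four weeks, respectively". In both arms session one lasts 40 minutes and sessions two and three about 20 minutes each.

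Under *Post-intervention data collection*, the first of three assessments labelled post-intervention covers knowledge and attitude only and takes place "immediately after the second session of the intervention is completed". The later visits are tied to it: "The 6-month post-intervention assessment will be conducted six months after the immediate post-intervention assessment", and "The 12-month post-intervention assessment will be conducted 12 months after the immediate post-intervention assessment". Oral examinations are done at those later visits and are explicitly left out of the immediate one.

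The *Data analysis plan* includes the immediate assessment among the time points for intervention effects over the study period. Its test-versus-control comparison over 12 months lists only baseline, 6 months and 12 months.

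The abstract gives a different length for the singing: "the participants will sing the song for two weeks".

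**The concern.** An assessment labelled post-intervention should follow the intervention. Here it comes while one session is still outstanding in each arm and, in the test arm, about two weeks of supervised daily singing as well. Reported under its present label, the early knowledge and attitude result would be read as the effect of the completed programme, which it is not.

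The same date starts the follow-up clock, so the 6- and 12-month visits are counted from a point inside the intervention.

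The abstract's two weeks of singing adds to the uncertainty, because it states the dose of the experimental intervention at about half of what the Methods prescribe. Two weeks of singing and an assessment after session two fit each other, but both conflict with the three-session, one-month course. A team working from the abstract and the data-collection section could run a different schedule from one working from the intervention section.

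**Working it through.** No sample size, power or alpha figure is involved. The check is a timeline, with session one as day 0.

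| Event | Day | Source in the Protocol article |
|---|---|---|
| Session one (40 min) | 0 | Intervention and control groups |
| Session two (20 min) | 14 | same |
| Immediate post-intervention assessment | 14 | Post-intervention data collection |
| Session three (20 min) | 28 | Intervention and control groups |
| End of daily singing, test arm | 28 to 30.4 | same |

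The end of singing is a range because *one month* can mean four weeks (28 days) or a calendar month (365.25 / 12 = 30.4 days).

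**Exposure at the immediate assessment**

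- Sessions, both arms: 2 of 3.
- Session minutes, both arms: (40 + 20) / (40 + 20 + 20) = 60 / 80 = 75%, with 20 / 80 = 25% still to come.
- Singing period, test arm only: 14 / 28 = 50%, or 14 / 30.4 = 46%.

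**Later visits counted from session three**

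- 6 months is 182.6 days; 182.6 − 14 = 168.6 days, and 168.6 / 30.4 = 5.5 months.
- 12 months is 365.25 days; 365.25 − 14 = 351.25 days, and 351.25 / 30.4 = 11.5 months (351.25 / 30.44 = 11.54 before rounding).

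The 14-day shift is the same in both arms.

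**Abstract against Methods**

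Two weeks against one month gives the same ratios as above: 14 / 28 = 50%, or 14 / 30.4 = 46%.

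**Where the immediate assessment is used**

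It is one of the three assessments labelled post-intervention. It measures knowledge and attitude, which the article lists as secondary outcomes. It enters the analysis of effects over the study period but is not among the time points listed for the test-versus-control comparison.

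**The case against.** The strongest reply is that little depends on this visit. It carries only secondary outcomes, includes no oral examination, falls on the same date in both arms, and is absent from the listed between-group comparison. All of that is correct, and it limits the weight of the point. It does not make the label or the date right.

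A second reply is that the dose percentages overstate what is missing. The songs, or the health talk, are delivered in session one, and the later sessions repeat or revise them. No new content is described for session three. This is fair: the percentages measure repetition still to come, not messages still untaught, and the article gives no basis for saying how far that repetition would change the scores. But repeated singing is part of the test intervention as specified, and the article describes no daily counterpart in the control arm. What is outstanding at week 2 is therefore not the same in the two arms, even though the session calendar is.

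Third, a two-week shift in the 6- and 12-month visits is small, equal across arms and openly stated. That stands; no consequence for the primary comparison can be shown.

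Finally, naming the second session may be a slip for the third, and the SPIRIT schedule and flow diagram (Figs 2 and 3), which were not available for this review, may show the intended timing. If so, the data-collection text still needs correcting, since a figure placing the visit at week 4 would contradict it.

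**Conclusion.** The concern holds. As written, one of the three assessments labelled post-intervention is a mid-intervention measurement at week 2 of 4, after 75% of session minutes in both arms and 46% to 50% of the singing period in the test arm. The 6- and 12-month visits fall about 5.5 and 11.5 months after the last session. The abstract separately understates the singing period by about half.

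The consequence is interpretive and confined to knowledge and attitude at one time point. The primary comparison is not biased by it, and the document supports no direction of bias for the early result. It should be corrected, but it does not threaten the trial's main conclusion.

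This rests on the text alone, on sessions held at days 0, 14 and 28, and on reading one month as 28 to 30.4 days. Whether week 2 was chosen deliberately or is a drafting error cannot be determined from the article. Either way the text needs a change.

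**What to change.** Preferred: in *Post-intervention data collection*, place the immediate assessment directly after the third session in both arms, and count the 6- and 12-month visits from there. The visit moves from about day 14 to about day 28, and the later visits then fall a full 6 and 12 months after the last session.

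Alternative, if week 2 is intended: call it a mid-intervention assessment wherever it appears, including the *Data analysis plan*, report it as such, and say explicitly that the later visits are timed from week 2 and not from the end of the intervention.

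In either case, change the singing period in the abstract to one month and check that Figs 2 and 3 agree with the corrected text.

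The cost is a wording correction, or one visit date moved by about two weeks with the later visits following. No visit is added and the sample size does not change.
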